### Blinding

The patients will not be informed of the group to which they are randomised. Concurrently, the clinician assessing the fracture reduction on the post-operative radiographs will be blinded to the arm of the trial to which the patient has been allocated. The surgeon operating on the patient will not be blinded as this is impossible, given they will be witness to whether or not intra-operative CT is performed. The physician assessing the patient in clinic at both 1 week and 6 weeks post-surgery will not be blinded to the patient’s study group. Blinding of this assessment would be extremely difficult as the physician assessing the patient will be involved with the operation and hence know the allocated group. The clinician assessing the post-operative radiographic reduction will not perform any of the operations in the trial.

### Study groups (control and intervention)

The intervention group will undergo CT during their operation to reduce the ZMC or ZA fracture. This scan occurs after the fracture has been opened, reduced and fixated or in the case of an isolated zygomatic arch fracture, after it has been opened and elevated. Once the scan has been completed the surgeon will review the scan and decide if the reduction is satisfactory. If they are satisfied with the reduction, the incisions will be closed and the operation completed. If there are inaccuracies with the reduction, the fixation equipment will be removed and the fractured bone adjusted to the correct position. It is then left to the discretion of the surgeon to decide if they wish to have another intra-operative CT scan or if they are clinically satisfied with the reduction. Once the surgery is completed, post-operative radiographs will be performed prior to the patient being discharged home. These radiographs will include a submental-vertex view (SMV), a posterior-anterior face (PA face) view and occipitomental 15° and 30° views (OM15 and OM30).

Patients in the control group will undergo their relevant surgery as normal but will not have any intra-operative imaging performed. After completion of the surgery, control group patients will undergo the same post-operative radiography as described for the intervention group. No other concomitant care or interventions are prohibited during the trial.

Surgical incisions are identical in both groups but are at the discretion of the operating surgeon. Direct access to fracture sites is via the upper blepharoplasty incision, subtarsal incision or upper buccal sulcus transoral incision. Elevation is either via a “Gillies” temporal incision or upper buccal sulcus incision.

All procedures will be performed by or under the direct in-theatre supervision of one of three Oral and Maxillofacial Specialist surgeons. All three have extensive experience in the management of facial trauma with each having a minimum experience of managing 300 hundred zygomatic complex fractures.

### Follow up and outcomes

All patients in the trial will have post-operative SMV, PA face, OM15 and OM30 radiographs taken either on the day of surgery or on the following day, prior to discharge. These radiographs will be assessed blinded to study group, by an oral and maxillofacial surgeon who will not be involved in any of the operations or pre-surgical or post-surgical clinical assessments. The adequacy of the fracture reduction will be based on the radiographs and the quality of the reduction will be evaluated as “good”, “fair” or “poor”:
Good: equivalent to premorbidFair: minor discrepancy but unlikely to require re-operationPoor: major discrepancy, re-operation required

Patients in the trial who are undergoing ZMC open reduction and internal fixation will stay overnight in hospital, and barring any complications will be discharged home on day 1 post-surgery. Patients undergoing open reduction of their isolated ZA fracture will be discharged on the same day as surgery, unless there are any unforeseen complications. All patients will be followed up in the OMFS outpatient department at 1 week and 6 weeks post-surgery. During these outpatient appointments, the registrar or consultant reviewing the patient will assess them for diplopia, surgical site scarring and facial profile restoration. These parameters will be graded by the OMFS registrar or consultant and their assessment will be recorded on a standardised form (Figs. 2 and 3). The need for revision surgery at any timepoint until 3 months following the completion of the study and a number of other variables (see Figs. 2 and 3 for a full list) will also be recorded on the form.

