**Fig. 2 Fig2:**
[figure not shown]
This is the post-operative assessment form that will be completed for all patients. It will be completed when the patient is reviewed in the outpatient department at one and six weeks post-operatively

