### Evaluation of outcomes

The two-sample *t* test will be used for analysis of continuous variables. The chi-square test will be used for analysis of categorical variables and for all data, a *p* value <0.05 will be considered significant. The software program SPSS will be used for all statistical analysis. Subgroup analysis based on the severity of the fractures will also be conducted. Patients will be analysed as per their treatment but non adherence will be considered in the final presentation of data. An interim analysis will be also be undertaken. There are no other audits of trial conduct planned.

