### Power calculation

An estimated 200 patients will be required for a sample size that will produce significant results. This is based on two-sided testing with a power calculation of 80% and is established from local department outcome estimates and results from studies by Van Hout et al., Hurrell et al. and Van Den Bergh et al. [10, 15, 16]. The variable that required the largest projected sample size to obtain a statistically significant result was the adequacy of post-operative fracture reduction as demonstrated radiographically. The power calculation was performed by [name], a biostatistician from the University of Queensland (UQ) School of Population Health.

Due to the low level of evidence available in the current literature, the sample size calculations may not be reliable and estimates were not possible for all variables being proposed in this study. Subsequently, a mid-study analysis will be conducted to more accurately assess the predicted sample size calculations. It is estimated that from the average number patients presenting yearly with ZMC and ZA fractures at the RBWH, this study will take approximately 2 years to complete. If the mid-study analysis identifies a statistically significant result, the study will potentially be terminated early. The decision to terminate the trial or continue after the mid-study analysis will be at the discretion of the study authors.

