## Trial status

The final version of the trial protocol is dated 5 April 2016. Recruitment for the trial began in August 2016 and is estimated to finish in September 2019.

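### Revision surgery is counted to a trial-wide date, so follow-up runs from about 3 to about 40 months per patient and the revision proportion is hard to interpret

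*Protocol article*

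**What the plan says.** - **Role of the outcome.** Study objectives lists the need for revision surgery among six variables that assess the primary objective. The stated aim of the trial also names revision rates.
- **Window.** Follow up and outcomes has the form record "The need for revision surgery at any timepoint until 3 months following the completion of the study". No section sets a window per patient, and completion of the study is not defined.
- **Visits and form.** "All patients will be followed up in the OMFS outpatient department at 1 week and 6 weeks post-surgery". The captions of Figs. 2 and 3 say of the form: "It will be completed when the patient is reviewed in the outpatient department at one and six weeks post-operatively". No later contact is described.
- **Calendar.** Trial status: "Recruitment for the trial began in August 2016 and is estimated to finish in September 2019". The Power calculation section had expected that "this study will take approximately 2 years to complete".
- **Test.** Evaluation of outcomes: "The chi-square test will be used for analysis of categorical variables".
- **Stopping.** Power calculation: "If the mid-study analysis identifies a statistically significant result, the study will potentially be terminated early", and "The decision to terminate the trial or continue after the mid-study analysis will be at the discretion of the study authors".

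**The concern.** A yes/no outcome tested by chi-square is easiest to read when every patient has been watched for the same length of time. Here the earliest patients can be counted as revised over more than three years and the latest over about three months. The reported percentage then averages 3-month risks, 40-month risks and everything between, with weights set by how fast patients were recruited. Two trials with the same surgery and the same revision risk would report different percentages if one recruited more slowly or stopped sooner. The figure is therefore difficult to compare with other reports or to use when counselling a patient.

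Two further points follow from the text. First, the window stays open for months or years, while the form that is to hold the information is completed for the last time at 6 weeks. Second, at a mid-study analysis the most recently operated patients would enter this outcome with almost no follow-up.

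**Working it through.** The article states no figure for length of observation, so there is none to reproduce. It can be derived from the dates.

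**Inputs**
- Recruitment August 2016 to September 2019 (Trial status): 37 months, or 36 to 38 depending on the days within the months.
- Cut-off 3 months after completion (Follow up and outcomes).
- Last scheduled visit at 6 weeks = 42/30.44 = 1.4 months.
- Planned duration about 2 years = 24 months (Power calculation).
- Assumptions: operation close to recruitment; uniform accrual for the means.

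**Observation time**

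Shortest = 3; longest = accrual + 3; mean = 3 + accrual/2.

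| Scenario | Shortest (months) | Longest (months) | Mean (months) |
|---|---|---|---|
| Completion = end of recruitment | 3 | 37 + 3 = 40 | 3 + 37/2 = 21.5 |
| Completion = last 6-week visit | 3 + 1.4 = 4.4 | about 42 at most | about 23 |
| The 2-year estimate | 3 | 24 + 3 = 27 | 3 + 24/2 = 15 |
| Stop after half the accrual time (assumed) | 3 | 18.5 + 3 = 21.5 | 3 + 18.5/2 = 12.25 |

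The longest window is 40 − 27 = 13 months longer under the Trial status dates than under the 2-year estimate, purely because recruitment takes longer.

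**Effect on the reported proportion (illustration; the rates are assumed)**

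Suppose 5% are revised by 3 months and a constant hazard of 0.2% per month follows. With D = longest − 3 and uniform accrual, the expected proportion is 1 − 0.95 × (1 − exp(−0.002 D))/(0.002 D).
- D = 18.5: 6.7%
- D = 24: 7.2%
- D = 37: 8.4%

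With no revisions after 3 months it is 5.0% in every case. The size of the problem therefore depends wholly on how many revisions come late, which the article does not say.

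**Effect on power (illustration; the rates are assumed)**

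Exact binomial power of the Pearson chi-square test, 100 per arm, two-sided 0.05. Early revision is 12% in controls and 2% with CT. Late revisions are independent of early ones, so each arm's total is 1 − (1 − early)(1 − late).

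| Late revisions, control / CT | Totals compared | Power |
|---|---|---|
| 0% / 0% | 12.0% vs 2.0% | 0.84 |
| 1% / 1% | 12.9% vs 3.0% | 0.78 |
| 3% / 3% | 14.6% vs 4.9% | 0.66 |
| 5% / 5% | 16.4% vs 6.9% | 0.57 |
| 10% / 10% | 20.8% vs 11.8% | 0.41 |
| 5% / 1% | 16.4% vs 3.0% | 0.93 |

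Late revisions unrelated to the allocated arm lower power. Late revisions that CT also prevents raise it. The documents do not show which applies.

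**Form against window**

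Follow up and outcomes says that revision up to the trial-wide date is entered on the form. The captions of Figs. 2 and 3 say that the form is filled in at 1 and 6 weeks. Even the patient with the shortest window, 3 months, has an open period after the last stated completion of the form. The section and the two captions must be reconciled.

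**The case against.** The strongest defence is that nothing here biases the comparison. Patients are randomised concurrently, so both arms have the same expected observation time, and an early stop shortens it equally in both. Counting events to a common close date is an ordinary design, and the chi-square test of the proportion revised by that date is valid. All of this stands. A reader might infer from the range of 3 to 40 months that the test between arms is invalid; the documents do not support that.

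A reader might also infer that late revisions must dilute the effect and cost power. This too is unsupported. The article gives no revision rates, early or late. The Background links poor reduction to asymmetry and poor profile restoration, either of which could lead to a later revision, so late events might differ by arm. Nor does the sample size rest on this outcome: the Power calculation section names radiographic reduction as the variable needing the most patients.

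Two other inferences go too far. One is that late revisions will be missed. The forms and the timeline figure are not shown, and patients are identified by hospital record number, so capture from records is possible; the article neither states nor excludes it. The other is that revision surgery would trigger early stopping. The article does not tie stopping to any one outcome, and it gives the mid-study analysis first a sample-size purpose.

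Finally, it may be said that the exact cut-point belongs in a fuller document. That would answer a missing window. Here the article states a window, and states it in a form that gives unequal follow-up. If completion was meant per patient (6 weeks plus 3 months, about 4.4 months for everyone), the problem disappears, but the sentence refers to the study and would still need correcting.

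**Conclusion.** The point holds as a cheap improvement. As written, the revision outcome has a trial-wide end date, which gives about 3 to about 40 months of observation per patient (about 4.4 to 42 if completion means the last 6-week visit). The range moves with accrual and with any early stop. The resulting proportion mixes unequal follow-up, is hard to interpret or compare, and at an interim look would include patients with almost no follow-up. The stated times for completing the form do not fit the window.

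This is a matter of what the proportion means, not of bias between arms. The range rests on the recruitment dates under Trial status and on operation close to recruitment; the means also assume uniform accrual. The practical effect is small if few revisions occur after 3 months. Any effect on power cannot be given a size or a direction from the documents.

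**What to change.** Define the outcome as revision surgery within one fixed time of that patient's own index operation. Three months would serve as an example, since every patient reaches it under the current cut-off. In addition:

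- Ascertain it from the hospital record at that time for every randomised patient whose data are retained (the Withdrawal section deletes the data of those who withdraw).
- Reconcile the Follow up and outcomes section with the captions of Figs. 2 and 3, so that it is clear where a revision after 6 weeks is recorded.
- In any interim analysis of this outcome, include only patients who have completed the window.
- Report later revisions descriptively by arm.

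If the long window is wanted, keep it, define completion of the study, record the date of each revision, and analyse time to first revision with censoring at data close in place of the chi-square test.

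The cost is a sentence or two in the outcome definition and one record check per patient. The downside of the fixed window is that later revisions leave the formal comparison, although they are still reported.

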**Fig. 2 Fig2:**
[figure not shown]
This is the post-operative assessment form that will be completed for all patients. It will be completed when the patient is reviewed in the outpatient department at one and six weeks post-operatively

**Fig. 3 Fig3:**
[figure not shown]
This is the post-operative assessment form that will be completed for all patients. It will be completed when the patient is reviewed in the outpatient department at one and six weeks post-operatively

### Data collection, management and confidentiality

Data from the post-operative radiographic assessments will be entered directly into the trial Excel spreadsheet. All data recorded on the post-operative assessment forms (Figs. 2 and 3) will be transferred to the trial Excel spreadsheet. This Excel file will be stored on a single, password-protected personal computer. At the completion of the trial, the Excel spreadsheet will be transferred to a password-protected computer within the OMFS department at the RBWH. It will be stored on this computer for 15 years. All hard copies of the consent and post-operative assessment forms will be stored in a designated trial folder, which will be stored in a locked room in the OMFS department at the RBWH. At the completion of the trial, this folder will remain in the OMFS department for 15 years. The final trial data set will only be accessible to the authors of the trial.

Data on patients’ names, date of birth, gender, address and occupation will not be collected. Patients will only be identified by their unique record number (URN), otherwise known as a medical record or hospital record number. The URNs will be removed from the data pool prior to statistical analysis.

### Withdrawal

Patients are entitled to withdraw from the trial at any stage. Their withdrawal will have no implications for their ongoing management. Any patient who elects to withdraw will have their trial data deleted and the data will not be used in the statistical analysis.

If trial participants fail to attend their 1-week or 6-week follow-up appointments, any of their previously recorded data will be included in the trial data set and analysed accordingly.

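### Automatic deletion of all data from any patient who withdraws discards outcomes already recorded, and can bias the comparison if withdrawal is related to outcome

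*Protocol article*

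**What the plan says.** The Withdrawal section of the protocol article sets two rules in adjacent paragraphs.

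- **Active withdrawal.** "Patients are entitled to withdraw from the trial at any stage". The consequence is fixed: "Any patient who elects to withdraw will have their trial data deleted and the data will not be used in the statistical analysis". Neither the timing of the withdrawal nor the patient's wishes about existing data alters this.
- **Missed 1-week or 6-week visit.** For these patients, "any of their previously recorded data will be included in the trial data set and analysed accordingly".

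Three other statements fix what has been recorded by the time a patient might withdraw.

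- Follow up and outcomes: all patients have "radiographs taken either on the day of surgery or on the following day, prior to discharge".
- Data collection, management and confidentiality: "Data from the post-operative radiographic assessments will be entered directly into the trial Excel spreadsheet".
- Follow up and outcomes: "All patients will be followed up in the OMFS outpatient department at 1 week and 6 weeks post-surgery". Revision surgery is recorded for longer still, up to 3 months after the study is completed.

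The Power calculation section names radiographic adequacy of reduction as the variable that needed the largest sample, and says: "An estimated 200 patients will be required for a sample size that will produce significant results".

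**The concern.** The radiographs behind the outcome that sized the trial exist within about a day of surgery, while the opportunity to withdraw runs through at least six weeks of follow-up. A patient who withdraws after grading has a complete value for that outcome, and the rule removes it. It also removes any revision or adverse outcome already recorded for that patient. This is an exclusion after randomisation, made once the result can be known.

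A link between withdrawal and outcome is plausible. The worst radiographic grade is defined by the need for a further operation, so a poor result can become apparent to the patient. If such patients withdraw more often, the retained data understate poor results and harms. Once the records are deleted, no later analysis can examine how much the exclusion mattered. The same loss reaches the mid-study analysis, which may lead to early termination.

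**Working it through.** **Inputs from the article.** Total sample size 200. The Power calculation section says: "This is based on two-sided testing with a power calculation of 80" per cent. The significance level of 0.05 comes from Evaluation of outcomes. No outcome rates, effect size, withdrawal rate or withdrawal allowance are given. Equal allocation is assumed. All rates below are assumptions for illustration.

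**1. The stated 200.** It can be neither reproduced nor refuted without rates. Under the usual two-proportion formula (pooled variance, two-sided 0.05, 80% power), these rates of an inadequate result all give 200 in total: 10% v 1.0%, 20% v 6.6%, 30% v 13.7%, 50% v 30.6%. With a continuity correction the same pairs need 220 to 242.

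**2. Power when deletion is unrelated to outcome.** With n per arm and p̄ the mean of the two rates,

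power = Φ{[√n·|p₁ − p₂| − 1.96·√(2p̄(1 − p̄))] / √(p₁(1 − p₁) + p₂(1 − p₂))}.

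For 30% v 13.6%, the pooled term is 1.96 × 0.5839 = 1.144 and the denominator is 0.572.

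| Deleted | Analysed | Calculation | Power |
|---|---|---|---|
| 0% | 200 | (1.640 − 1.144)/0.572 | 80.7% |
| 5% | 190 | (1.598 − 1.144)/0.572 | 78.6% |
| 10% | 180 | (1.556 − 1.144)/0.572 | 76.4% |
| 20% | 160 | (1.467 − 1.144)/0.572 | 71.3% |

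The loss is about 2 points at 5% and 4 points at 10%. If deletion stays and 200 analysed patients are wanted, enrolment is 200/(1 − d), rounded up: 205, 211, 223 or 250 for d = 2%, 5%, 10% or 20%.

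**3. Bias.** If a share w_p of patients with an inadequate result and a share w_o of the others are deleted, the rate seen in the retained data is

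p(1 − w_p) / [p(1 − w_p) + (1 − p)(1 − w_o)].

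*No true effect, 20% in both arms:*

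- 10% deleted regardless of outcome: 20% v 20%, difference 0.
- w_p = 20%, w_o = 5% in both arms: 0.16/(0.16 + 0.76) = 17.4% in each arm, difference 0.
- w_p = 20% in control only, 5% for everyone else: control 17.4%, CT 20.0%. This is a false difference of 2.6 points, against CT.

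*True effect, 20% v 7.1% (difference 12.9 points), w_p = 20% and w_o = 5% in both arms:*

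- Control: 0.16/0.92 = 17.4%.
- CT: 0.0568/(0.0568 + 0.88255) = 6.0%.
- Observed difference: 0.1739 − 0.0605 = 0.1134, or 11.3 points.

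In this last example 92.0 and 93.9 patients per 100 remain, so about 7% of the 200 are deleted. Power falls from 76.4% (this pair with all 200 analysed) to 67.5%. That exceeds the loss from numbers alone, because the deletions fall mostly on the informative results.

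**The case against.** Several points on the other side are sound.

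- **Bias is possible, not shown.** A reader might infer that the rule biases the trial. Two of the three no-effect cases above give exactly zero. Patients are not told their arm, which lowers the risk that withdrawal differs between arms, though it does not hide a bad result from them.
- **Falling below 200 is not shown.** A reader might infer that deletions take the trial below its stated size. The Power calculation section does not say whether 200 counts patients enrolled or analysed, it plans a mid-study reassessment of the number, and a condensed article may leave an allowance to the full protocol.
- **Intention-to-treat analysis is not lost through this rule alone.** Evaluation of outcomes already says patients are analysed according to their treatment. That is a separate matter.
- **The two Withdrawal paragraphs do not contradict each other.** Choosing to withdraw and missing an appointment are different consent events, and deletion on request can be legitimate. The defect is that deletion is automatic.
- **The grading date is not stated.** Only the radiographs are dated, so only withdrawals after grading lose a recorded grade.
- **The practical reach is limited.** Recruitment began in August 2016 and was expected to end in September 2019, so new wording helps only later participants.

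These points limit the size and certainty of the harm. They do not remove the rule, which is explicit. A separate analysis plan could not repair it, because it cannot analyse records that have been deleted.

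**Conclusion.** The concern holds in a limited form. Followed as written, the rule irreversibly excludes randomised patients whose key outcome, revision or adverse outcome may already be recorded, although the next paragraph accepts partial data as usable. It can bias the comparison if withdrawal is related to outcome. Under no true effect it must also act differently by arm; under a true effect, equal action in both arms is enough to shrink the absolute difference.

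The 11.3 and 2.6 point results rest on assumed rates of 20% and 7.1% and assumed deletion shares of 20% and 5%. The power loss of 2 to 4 points rests on an assumed 5 to 10% deletion unrelated to outcome. The article supports none of these rates, so the actual bias is unknown and may be zero. What is certain is that the rule discards usable data and prevents any later check on the effect of doing so.

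**What to change.** Replace the deletion rule with wording such as:

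> Withdrawal ends further trial follow-up. Data collected up to withdrawal are retained and analysed unless the patient specifically asks for their deletion. Withdrawals and deletion requests are reported by arm with timing.

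Align the participant information and consent form. Apply the new rule to participants consented under it. Those consented earlier keep the deletion right they were given unless they agree otherwise. For them, report at least the number of withdrawals by arm and when they occurred, so that readers can judge the possible selection.

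The cost is protocol and consent wording with notification to the ethics committee and the registry. No extra data collection is needed. Where the new rule applies and no deletion is requested, a withdrawal after grading costs the radiographic analysis nothing.
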